### Statistical methods

#### Sample size

The sample size calculation is based on the assumption that the mean difference in weight after 10 weeks between the empagliflozin arm and the CRT arm will be − 3.2 Kg. We assumed that the weight will not change in the CRT only group (body composition may change) and, based on the literature, that empagliflozin treatment causes a reduction in weight of ≈ 3–3.5 Kg. For 80% power and significance level of 5% each arm should include 40 subjects (*n* = 120 total). Another calculation was based on ANOVA for the comparison of three groups. We assumed that body fat % at the end of study will be 37, 36 and 40% for the diet, drug and CRT arms, respectively, with a 6% SD in each group. These assumptions are based on unpublished data obtained in a pilot study conducted in the IEMH. Assuming an attrition of ~ 10% we intend to recruit 120 up to 140 participants. Power calculations were performed using the G*Power Statistical Power Analyses for Windows [53].

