#### Primary aims and hypotheses

##### Aim

To evaluate the short-term efficacy (10–20 weeks) of CRT, a V-Med diet separately or in combination with CRT, or empagliflozin separately or in combination with CRT, on the body weight, body composition and functional status in community dwelling older subjects with T2DM.

##### Hypothesis 1

We expect that the increase in lean body mass (LBM) will be superior in the CRT arm vs. the other groups after 10 weeks. After 20 weeks the relative increase in LBM will be higher in the V-Med diet + CRT compared to the empagliflozin + CRT group.

##### Hypothesis 2

We expect that the functional status would improve the most in the CRT arm vs. the other groups after 10 weeks. After 20 weeks, functional improvement will be larger in the combined therapy of V-Med diet + CRT as compared to the empagliflozin + CRT combination.

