## Methods/design

### Trial design

This is a single center, open label, parallel group, exploratory clinical trial of CRT for 10 weeks; V-Med diet for 10 weeks and then CRT on top of diet for 10 weeks; empagliflozin 10 mg/day for 10 weeks and then CRT on top of drug therapy for 10 weeks (Fig. 1) in older subjects with T2DM. This trial will be conducted in conformance with Good Clinical Practices (GCP). The duration of the trial will be up to 25 weeks (with up to 8 clinic visits) for each subject. This will include a 1-week screening period (Visit 1 to Visit 2); a 10-week single treatment period (Visit 2 or 3 to Visit 6); a 10-week combination treatment period. Approximately 120 subjects ≥65 years of age with T2DM, diagnosed in accordance with American Diabetes Association guidelines and who meet all enrollment criteria will be randomized. The study will be conducted between May 2018 to September 2020. Information on the trial is disclosed at clinicaltrail.gov (trial no. NCT03560375). The trial will be disclosed according to the requirements of the International Committee of Medical Journal Editors (ICMJE) [32]. This study was approved by the Tel-Aviv Sourasky Medical Center Institutional Review Board. Any important protocol modifications will be reported for approval of the Institutional Review Board.

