##### Data handling

Data will be entered by AB. Quality control will be performed routinely by three students (AB, OK, and AR) using double data entry and range checks for data values. Analysis will be performed by SPSS software (IBM SPSS Statistics for Windows, Version 24.0; IBM Corp.). *P* values will be compared to the value of *p* = 0.05 or less (taking into account multiple comparisons using the Benjamini-Hochberg [54]).

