##### Baseline comparisons

To test differences in continuous variables between the study groups the one-way analysis of variance (ANOVA) test will be performed (or Kruskal–Wallis one-way analysis of variance when normal distribution is rejected). For comparison of dichotomous or categorical variables the Chi square test will be performed.

The primary endpoints (% change in LBM and change in weight) will be analyzed using the analysis of covariance (ANCOVA) after 10 weeks and after 20 weeks (for diet and drug arms only) including several factors and covariates. Table 2 indicates the list of covariates and factors. Table 3 indicates the different outcomes and appropriate statistical method.

**Table 2 Tab2:** List of potential covariates and factors (partial list)

Factor or covariate	Type	Defined as
Treatment	Factor	SGLT2 inhibitor, diet, CRT
GLP1 agonists	Factor	Yes, no
Baseline body weight/ BMI	Covariate	–
HbA1c (%)	Covariate	–
Caloric consumption (Kcal)	Covariate	–
Resting metabolic rate (Kcal)	Covariate	–
Body fat %	Covariate	–
Strength (kg)	Covariate	–
Frailty or sarcopenia status	Factor	Frail or sarcopenic, pre-frail or pre sarcopenic and robust

*Abbreviations*: *BMI* Body Mass Index, *CRT* Circuit Resistance Training, *GLP-1* Glucagon-Like Peptide-1, *HbA1c* Hemoglobin A1C

**Table 3 Tab3:** The different outcomes and appropriate statistical method (partial list)

	Endpoint type	Statistical method
Primary outcome		
Change in body weight (%) from baseline to 10 weeks or to 20 weeks	Continuous	ANCOVA
Change in % lean body mass from baseline to 10 weeks or to 20 weeks	Continuous	ANCOVA
Proportion of participants having lost ≥2.5% at week 10 and 20	Binary	Logistic regression
Secondary outcomes		
Change in waist circumference from baseline to 10 weeks or to 20 weeks	Continuous	ANCOVA
Change in FPG and HB1Ac from baseline to 10 weeks or to 20 weeks	Continuous	ANCOVA
Change in sarcopenia and frailty status (improved vs. not improved; change from one level to the other) at week 10 and 20	Binary	Logistic regression
Change in strength and other functional abilities from baseline to 10 weeks or to 20 weeks	Continuous	ANCOVA
Change in systolic blood pressure from baseline to 10 weeks or to 20 weeks	Continuous	ANCOVA
Change in quality of life (improved vs. not improved; change from one level to the other) at week 10 and 20	Binary	Logistic regression

*Abbreviations*: *ANCOVA* Analysis of Covariance, *FPG* Fasting Plasma Glucose, *HbA1c* Hemoglobin A1C

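### The 80% power claim has no attrition allowance at the 120 given as the number randomised (about 74–76% there), is stated for an unadjusted 5% test, and sits beside a primary set that differs between sections

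*Protocol article*

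**What the plan says.** All references are to the protocol article.

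- **Sample size.** The first calculation assumes a 3.2 kg difference in weight between empagliflozin and CRT at 10 weeks and concludes "For 80% power and significance level of 5% each arm should include 40 subjects" (120 in total). No SD for weight is given. A second calculation, a three-group ANOVA on end-of-study body fat, assumes means of 37, 36 and 40% with SD 6, but reports no resulting sample size or power. The section then says "Assuming an attrition of ~ 10% we intend to recruit 120 up to 140 participants".
- **Number randomised.** The Abstract gives 120. Trial design gives "Approximately 120 subjects ≥65 years of age with T2DM". Neither mentions an upper figure.
- **Significance level in the analysis.** Data handling compares p values with 0.05, "taking into account multiple comparisons using the Benjamini-Hochberg".
- **Primary set.** Under the primary aims, Hypothesis 1 concerns lean body mass (LBM) and Hypothesis 2 functional status: "We expect that the functional status would improve the most in the CRT arm vs. the other groups after 10 weeks". The analysis text under Baseline comparisons names percentage change in LBM and change in weight. Table 3 lists three primary outcomes, the third being "Proportion of participants having lost ≥2.5% at week 10 and 20", and places "Change in strength and other functional abilities from baseline to 10 weeks or to 20 weeks" among the secondary outcomes.

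**The concern.** The number derived as needed for 80% power is also the number to be randomised, although the same section expects to lose a tenth of the participants. If recruitment stops at the figure in the Abstract and Trial design, the trial does not have the power it claims.

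Two further features make the claim hard to interpret. The sizing uses 5% for a single comparison, whereas the analysis adjusts for multiplicity. The outcomes that count as primary change from section to section, so it is unclear to which tests the 80% and the adjustment apply. At the end of the trial, any of LBM, weight, the responder proportion or function could be presented as a primary result with some support in the text.

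**Working it through.** **Inputs from the document.** Weight difference 3.2 kg; power 80%; significance 5%; 40 per arm; body-fat means 37, 36 and 40% with SD 6; attrition about 10%; allocation 1:1:1; recruitment 120–140.

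**Assumptions added here.** Two-sided tests. The weight SD is not stated, so it is solved from the plan's own result.

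**1. The plan's figure for weight.** It cannot be reproduced directly without an SD. For a two-sample t test with n = 40 per arm, two-sided 5% and 80% power, the standardised difference is d = 0.634. The implied SD is 3.2 / 0.634 = 5.04 kg.

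**2. The ANOVA.** The mean of 37, 36 and 40 is 37.67. The root-mean-square deviation of the three means from it is 1.700, so f = 1.700 / 6 = 0.283. At 120 analysed, the noncentral F distribution gives 78.9%, close to 80%. In equal arms, 123 analysed gives 79.96% and 126 gives 81.0%, so a strict 80% takes 42 per arm.

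**3. Attrition.** 120 × 0.9 = 108, or 36 per arm. To keep 40 per arm: 40 / 0.9 = 44.4, rounded up to 45 per arm, or 135 randomised. To keep 42 per arm: 126 / 0.9 = 140 randomised.

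**4. Power at an unadjusted 5%.**

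| Randomised | With end-of-study data | Weight (SD 5.04 kg) | Body-fat ANOVA |
|---|---|---|---|
| 120 | 108 (36 per arm) | 75.6% | 74.1% |
| 135 | 121.5 (40.5 per arm) | 80.5% | 79.4% |
| 140 | 126 (42 per arm) | 81.9% | 81.0% |

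The weight column depends on the inferred SD. At 36 per arm it would be 92% with SD 4 kg, 76% with SD 5 kg and 61% with SD 6 kg.

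**5. Effect of Benjamini-Hochberg.** With m endpoints, the smallest p value is compared with 0.05/m if it is the only one to succeed. If every endpoint in the family has p ≤ 0.05, the threshold stays at 0.05 and nothing is lost. The worst case for one endpoint is:

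| Endpoints | Threshold | Weight, 36 per arm | ANOVA, 36 per arm | Weight, 42 per arm | ANOVA, 42 per arm |
|---|---|---|---|---|---|
| 2 | 0.025 | 65.6% | 64.0% | 73.3% | 72.3% |
| 3 | 0.0167 | 59.6% | 58.0% | 67.8% | 66.9% |

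**6. The primary set, side by side.**

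| Outcome | Hypotheses under the primary aims | Analysis text | Table 3 |
|---|---|---|---|
| LBM | yes | primary | primary |
| Weight | named in the aim, no hypothesis | primary | primary |
| Loss of ≥2.5% | no | no | primary |
| Functional status | yes (Hypothesis 2) | no | secondary |

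Only LBM is treated as primary in all three places and also carries a hypothesis.

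**The case against.** The strongest reply is that the plan does allow for attrition: it links the 10% to a range, and the top of that range works. At 140 randomised, 42 per arm remain, and both calculations exceed 80%. In fact 140 is exactly the ANOVA requirement inflated for attrition (126 / 0.9). This stands. A reader might infer that the plan cannot deliver 80%, and the document does not support that. The defect is confined to the lower part of the range and to the 120 repeated without qualification elsewhere.

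Other points on that side also carry weight:

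- **Dropouts are not removed from the analysis.** The primary analysis imputes the last available observation, so 108 is the number with end-of-study data and not the number analysed. Imputation probably dilutes the effect, so it cannot be counted on to restore the lost power. Covariate adjustment by ANCOVA could raise power, by an amount the document does not allow one to calculate.
- **The multiplicity loss is a range.** One could count many pairwise tests and time points and arrive at a much lower power, but the article defines no such family, and that detail may properly sit in an analysis plan not shown here. The worst case also needs a single positive endpoint, which is unlikely for weight if the responder outcome, itself a dichotomy of weight loss, is in the family.
- **LBM is not wholly without a sample-size basis.** The lean outcome is built from the proportion of lean mass in body weight, and body fat % is largely its complement, though the ANOVA uses end-of-study values and not relative change. Functional status has no such basis.
- **The trial is described as exploratory.** That lowers the stakes, but the article still claims 80% power and names primary outcomes.

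**Conclusion.** The concern holds in a limited form. At the 120 given in the Abstract and Trial design, with the plan's own 10% attrition, power at an unadjusted 5% is about 74% for the body-fat ANOVA and about 76% for weight, a shortfall of 4 to 6 percentage points. The claim is met from about 135 randomised for weight and at 140 for both calculations, inside the range already stated.

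The ANOVA figure rests on the document's own inputs. The weight figure rests on an SD inferred from the claim under test and on a two-sided test, so it shows what 36 per arm implies if the claim is right at 40. Both treat the roughly 10% lost as contributing no information.

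The further loss from Benjamini-Hochberg lies between none and the worst case shown. It cannot be narrowed while the primary set is unsettled. The conflict over that set does not depend on any calculation: the hypotheses, the analysis text and Table 3 give three different lists, and an unseen analysis plan would not remove a contradiction within this document.

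**What to change.** 1. **One randomised number.** In the Abstract, Trial design and Sample size, either keep 120 and state that about 108 are expected to complete, with power of about 74–76%, or use the upper part of the range: about 135 for 80% on weight alone, 140 for both calculations.
2. **The weight SD.** State the SD actually used and whether the test is two-sided. The 5.04 kg above is an inference and should not be entered as the investigators' assumption.
3. **Dropouts.** Note that last-observation imputation keeps them in the primary analysis but probably dilutes the effect, so that the completer number and the analysed number are not confused.
4. **One primary set.** Use the same list in the hypotheses, the analysis text and Table 3. One option is the pair the text already names, LBM and weight, at week 10, with the responder and functional outcomes secondary. This keeps LBM, the subject of Hypothesis 1, as primary.
5. **Matching alpha.** State power at the significance level that applies to that set under Benjamini-Hochberg, or say explicitly that the sizing is for a single unadjusted test.

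The cost is mostly wording: a less favourable power figure, or 15 to 20 more participants than 120 within the range already planned, and fewer outcomes called primary.

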#### Definition of main outcomes

Relative lean mass change will be calculated as % lean mass (the proportion of lean mass out of weight) at the end of study minus % lean mass at baseline divided by lean mass % at baseline and multiplied by 100. Change in body weight (%) will be calculated as body weight at the end of 10 weeks (and 20 weeks) minus baseline body weight divided by body weight at baseline and multiplied by 100.

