### Main ascertainment of response variables

#### Anthropometric and sarcopenia

Anthropometric measurements will be obtained following a uniform protocol. Height, weight, waist and hip circumference will be measured twice. LBM, skeletal muscle mass (SMM), fat mass (FM) and % fat will be evaluated by the direct segmental multi-frequency bioelectrical impendence analysis (BIA) technique method using the ‘In-Body 770 body composition analyzer’. The In-Body 770 is a valid tool for the assessments of total body and segmental body composition [40]. Sarcopenia will be assessed in line with the consensus definition offered elsewhere [41] using three parameters: a) low skeletal muscle mass; b) low muscle strength; c) low physical performance [41]. Pre-sarcopenia will be defined as low skeletal muscle mass but normal strength and physical performance, whereas sarcopenia will be defined as having both low muscle mass with either low muscle strength or low physical performance. Severe sarcopenia will be determined by the presence of all 3 criteria (low muscle mass + strength + low performance). Skeletal muscle mass will be obtained by the In-Body (770) body composition analyzer. Shortly, the skeletal muscle index (SMI = skeletal muscle mass/body mass × 100) will be compared to gender-specific reference norms of young adults (aged 18–39 years). Sarcopenia will be defined as any value < 10.76 kg/m^2^ for men and < 6.76 kg/m^2^ for women [42]. Low muscle strength and low physical performance will be assessed using grip strength and gait speed test as described in the following paragraph on frailty.

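### The primary lean-mass endpoint is lean mass as a share of body weight, while Hypothesis 1 at week 10 concerns lean mass itself; with weight loss expected in one arm and not in another, the two can rank the arms differently

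*Protocol article*

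**What the plan says.** Hypothesis 1 (Primary aims and hypotheses) has two parts. At week 10: "We expect that the increase in lean body mass (LBM) will be superior in the CRT arm vs. the other groups after 10 weeks". At week 20: "After 20 weeks the relative increase in LBM will be higher in the V-Med diet + CRT compared to the empagliflozin + CRT group".

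Definition of main outcomes sets the scoring rule: "Relative lean mass change will be calculated as % lean mass (the proportion of lean mass out of weight) at the end of study", minus the baseline share, divided by the baseline share, times 100. The quantity followed is thus LBM divided by body weight.

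The primary endpoint is then named in two ways within one section (Baseline comparisons). The text has "The primary endpoints (% change in LBM and change in weight) will be analyzed", which reads as a change in the mass. Table 3 has "Change in % lean body mass from baseline to 10 weeks or to 20 weeks", which is a change in the share and agrees with Definition of main outcomes.

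Lean mass is measured directly by bioelectrical impedance (Anthropometric and sarcopenia): "LBM, skeletal muscle mass (SMM), fat mass (FM) and % fat will be evaluated". Neither Definition of main outcomes nor Table 3 lists change in that mass as an endpoint.

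Sample size assumes a 3.2 kg weight difference between empagliflozin and CRT at week 10, with CRT weight unchanged. It also states: "We assumed that body fat % at the end of study will be 37, 36 and 40% for the diet, drug and CRT arms", with an SD of 6%.

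**The concern.** Body weight is the denominator of the endpoint, and the plan expects it to move in one of the two arms that it sizes on weight and not in the other. The share rises whenever the lean part of the weight lost is smaller than the baseline lean share. An arm can therefore score a gain while its lean kilograms fall.

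Hypothesis 1 predicts that CRT adds more lean mass than the other arms. On the share, a weight-losing arm can rank above CRT even when CRT gained lean kilograms and that arm lost them. In older adults, for whom the article is concerned with sarcopenia, a reader would take such a result as evidence about muscle when it may reflect fat loss.

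**Working it through.** **The plan's own figure.** The stated size is 40 per arm for 80% power at 5%.

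- Weight basis: no SD is given. A two-sided t test with a difference of 3.2 kg and 40 per arm implies an SD of about 5.0 kg, so the figure cannot be confirmed.
- Body-fat basis: means 37, 36 and 40 with SD 6 give f = √[(0.667² + 1.667² + 2.333²)/3] / 6 = 0.283. ANOVA power at 120 is 78.9%, compatible with the stated 80%.

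Neither calculation is on LBM in kg. The endpoint problem does not depend on the sample size.

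**Inputs for the endpoint check.**

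- From Sample size: weight change −3.2 kg on the drug and 0 kg on CRT.
- Assumed, because the article gives no values: baseline 80 kg, 60% lean (48 kg), and a CRT gain of 0.8 kg lean at stable weight. The lean part *s* of the drug arm's loss is varied from 0 to 40%.

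**Formula** (Definition of main outcomes): score = (end LBM / end weight) / (baseline LBM / baseline weight) − 1.

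**CRT:** (48.8 / 80) / 0.60 − 1 = 0.610 / 0.60 − 1 = +1.7%.

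**Drug arm, end weight 76.8 kg:**

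| *s* | Change in LBM | End share | Score |
|---|---|---|---|
| 0% | 0 kg | 48.00 / 76.8 = 62.5% | +4.2% |
| 25% | −0.80 kg | 47.20 / 76.8 = 61.5% | +2.4% |
| 36% | −1.152 kg | 46.848 / 76.8 = 61.0% | +1.7% (tie) |
| 40% | −1.28 kg | 46.72 / 76.8 = 60.8% | +1.4% |

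In kilograms CRT leads in every row. On the share, the drug arm leads when *s* is below 36%, and CRT leads when it is above. The crossover solves (48 − 3.2*s*) / 76.8 = 0.610, so *s* = 1.152 / 3.2 = 0.36.

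**How much CRT must gain to tie.** Gain = 80 × (48 − 3.2*s*) / 76.8 − 48. At *s* = 25% this is 1.17 kg. Over baselines of 70 to 90 kg, 60 to 63% lean and *s* from 0 to 30%, CRT needs about 1.0 to 2.1 kg more lean mass just to tie with a drug arm that gained none or lost up to 0.96 kg.

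**The planning fat values.** Taking the lean share as 100 minus fat % (an approximation), 37/36/40% becomes about 63/64/60% for diet, drug and CRT. From any common baseline, CRT ranks last on the share. With an assumed baseline of 60% lean the scores are (63 − 60)/60 = +5.0%, (64 − 60)/60 = +6.7% and 0.0%; with 62% they are +1.6%, +3.2% and −3.2%.

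**The case against.** A measure relative to weight may be deliberate. The aim names body composition, the week-20 part of Hypothesis 1 speaks of a relative increase, the skeletal muscle index in Anthropometric and sarcopenia is also scaled to body mass, and Table 3 agrees with Definition of main outcomes. This stands as a reason to keep the share as an outcome. It does not reconcile the share with the week-10 part of Hypothesis 1 or with the endpoint as named in the text.

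Body weight is also a primary endpoint and LBM is recorded, so kilograms can be recovered: (1 + share change)(1 + weight change) − 1. At *s* = 25%, 1.0243 × 0.96 − 1 = −1.7%. The trial is also labelled exploratory. A misleading result could therefore be noticed, but the tested lean-mass endpoint would still be the share. Adjusting for baseline weight (Table 2) does not remove weight change after randomisation.

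Three stronger readings are tempting, and the article does not support them:

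- *The order must reverse.* The example rests on assumed inputs, and the reversal disappears above 36%. If the lean part of the loss equals the baseline lean share, the ratio does not move at all; and a large enough CRT gain still ranks first.
- *The planning fat values show that Hypothesis 1 will fail at week 10.* They refer to the end of study, which may mean week 20 for diet and drug, after CRT was added. The week-10 weight assumptions point in the same direction but do not fix the ranking.
- *CRT at week 10 is compared with the other arms at week 20.* The primary-endpoint text sets the analysis at week 10, and at week 20 for diet and drug only. The end-of-study wording in Definition of main outcomes is merely loose.

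**Conclusion.** The point holds in this form: the primary lean-mass endpoint is worded inconsistently, and its defined version measures a different quantity from the week-10 hypothesis. Under the plan's own weight assumptions the share favours the arm that loses weight, unless the lean part of that loss reaches the baseline lean share.

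In the illustration the drug arm scores +4.2% to +1.4% against +1.7% for CRT, with a crossover at 36%. Those figures depend on an assumed baseline of 80 kg and 60% lean and an assumed CRT gain of 0.8 kg; the weight changes are the article's. That CRT ranks last on the planning fat values needs only a common baseline and the approximation of lean share as 100 minus fat %, but its time point is uncertain. The endpoint can mislead about kilograms; it need not.

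**What to change.** - Define the primary lean-mass endpoint for Hypothesis 1 as change, or % change, in LBM in kg. Analyse it by ANCOVA adjusted for baseline LBM and gender, at week 10 for all arms and at week 20 for diet + CRT against empagliflozin + CRT.
- Keep lean mass as a share of weight as a secondary body-composition outcome.
- Use the same definition in Hypothesis 1, Definition of main outcomes, the primary-endpoint text and Table 3, and name the weeks in place of the end of study.

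No new measurement is needed, since the impedance device already provides LBM. The cost is more than wording. The stated sample size rests on weight and on body fat %, the latter roughly the complement of the lean share, and gives no difference or SD for LBM in kg. The plan should say that its power calculation does not cover LBM in kg. The expected difference on that scale may also be smaller.
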